## Abstract

**Background:**

Persistent infection of high-risk human papillomavirus (HPV) can lead to cervical intraepithelial neoplasia, cervical cancer, and even death. HPV vaccination for girls aged 9-14 years can effectively prevent the occurrence of cervical cancer. Some Chinese provinces and cities have launched free HPV vaccination programs for school-age girls; however, due to the lack of supportive government policies, the high price and supply shortage of HPV vaccines, and vaccine hesitancy, some parents refuse to vaccinate their daughters.

**Objective:**

This protocol reports the design of a randomized controlled trial (RCT) aiming to explore the efficacy of a digital HPV vaccination education intervention based on the information-motivation-behavioral skills (IMB) model in improving the HPV vaccination rate among 11-13-year-old girls in central and western China.

**Methods:**

A multicenter intervention study based on an online applet will be conducted in December 2024, and about 750 eligible parents of 11-13-year-old girls will be assigned in a 1:1 ratio to an intervention group receiving 7-day digital HPV vaccination education based on the IMB model or a control group using non-HPV publicity materials. Free HPV vaccination pilot projects will be carried out among this population by our research team in central and western China (some parents might refuse to vaccinate their daughters). All participants will be asked to complete online questionnaires at baseline; postintervention; and 1 week, 1 month, and 3 months after the intervention.

**Results:**

The primary outcome of this study will be receipt of the first HPV vaccination within 3 months. Data will be analyzed based on an intention-to-treat approach, and Stata 16.0 will be used for statistical analysis.

**Conclusions:**

This study aims to improve the HPV vaccination rate among 11-13-year-old girls and will examine the impact of a digital HPV vaccination education intervention based on the IMB model. The findings of this study may offer promising intervention measures for HPV vaccine hesitancy in low-health-resource areas in the future.

**Trial Registration:**

Chinese Clinical Trial Registry, ChiCTR2300067402; https://tinyurl.com/v5zt4hc9

**International Registered Report Identifier (IRRID):**

PRR1-10.2196/58873

## Introduction

Human papillomavirus (HPV) is one of the most common sexually transmitted infections that can cause various genital diseases among women [1]. Persistent high-risk HPV infection is closely associated with the occurrence of cervical and other cancers [2]. According to the worldwide cancer statistics released by the International Agency for Research on Cancer, there were 604,000 new cases of cervical cancer and 342,000 deaths due to cervical cancer in 2020 worldwide [3]. The incidence of cervical cancer ranked third among malignant tumors, and the estimated death toll ranked second among deaths due to malignant tumors in Chinese women aged 15-44 years in 2020 [3]. In the past decade, the incidence and mortality of cervical cancer in China have shown an upward trend year on year [4]. Overall high-risk HPV infection rates in mainland Chinese women are about 19.0%, with subtypes 16, 52, 58, 53, and 18 being the most common infections [5].

Cervical cancer is considered near completely preventable through the primary and secondary prevention measures of HPV vaccination and screening [6]. In November 2020, the World Health Organization (WHO) released the *Global Strategy to Accelerate the Elimination of Cervical Cancer as a Public Health Problem* [4]. The WHO position paper recommended that young adolescent girls aged 9-14 years be the primary target group for HPV vaccination [7]. Relevant clinical trials and cohort studies have verified the safety and efficacy of HPV vaccines among this population [8]. In some high-income countries, the incidence of cervical cancer apparently decreased 10-12 years after widespread HPV vaccination [9,10]. However, effective prevention strategies were not applied adequately, with only 15% of girls of the target age vaccinated with the full course of HPV vaccines in 2019 [11]. In China, the HPV vaccination rate among girls aged 9-14 years was less than 1% in 2020, which is lower than the current world average of 20% [12,13]. As a result, improving the HPV vaccination rate among girls is an urgent need in China.

Chinese authorities approved HPV vaccines in 2016 [14]. Since 2020, some provinces and cities in China, especially those with good financial status, such as Guangdong Province and Fujian City, have launched free HPV vaccination programs for school-age girls [15]. However, without supportive government policies, the high price and supply shortage of HPV vaccines have impacted accessibility and affordability in the central and western regions of China [16,17]. In addition to the financial considerations and accessibility issues, vaccine hesitancy is also a major barrier to vaccine coverage [18]. Vaccine hesitancy is defined as the refusal or delay of vaccination when immunization services are available, which means low vaccine acceptance despite the availability of vaccination services [16]. Given the young age of the HPV vaccine target population, this study will focus on HPV vaccine hesitancy among the parents of girls aged 9-14 years. A recent study in mainland China reported that 53.9% of the guardians of secondary school girls aged 12-19 years were HPV vaccine hesitant, mainly because of a lack of knowledge of HPV vaccines and insufficient communication from reliable sources of information [19]. Previous studies have demonstrated that health interventions targeting parents can effectively improve vaccine coverage among girls. In 2018, an intervention using health education manuals and reminder letters was implemented among parents of 11-12-year-old girls in New York State, which increased the HPV vaccination rate from 24.1% to 75% [20]. Research on East African immigrant mothers conducted 10 HPV vaccine–related health education forums to increase HPV vaccine–related knowledge, improve attitude, and increase the intention to vaccinate adolescent children. Results from this study showed that mothers who attended the forums showed a more positive attitude and an intention to getting their daughters vaccinated [21]. Therefore, vaccine hesitancy has been shown to be a major obstacle to HPV vaccination among targeted girls.

In 2023, our research team initiated a free HPV vaccination pilot project among low-health-resource areas in China, which may last for at least 2 years, aiming to provide girls aged 11-13 years with HPV vaccines. Considering the possible HPV vaccine hesitancy among parents, this study will use an intervention for parents to improve their vaccination intention and increase the vaccination rate among their daughters, guided by the information-motivation-behavioral skills (IMB) model. The IMB model is a validated approach to predicting and promoting health behavior performance by providing relevant information, personal and social motivation, and behavioral skills [22,23]. It has been widely used in behavior interventions over the past decade among different populations, such as HIV prevention among Indian truck drivers, improvement of maternal breastfeeding efficiency in pregnant women with hepatitis B virus (HBV) infection, and antiretroviral therapy (ART) adherence improvement among HIV-positive patients in southwestern China [24-26]. In terms of HPV vaccine interventions in China, the IMB model has been proven to effectively increase the willingness of HPV vaccination, when combined with an online program [27]. This study will use the IMB model, which asserts that information related to HPV infection and cervical cancer prevention, HPV vaccination motivation, and behavioral skills are fundamental determinants of HPV vaccination (Figure 1) [28].

**Figure 1 figure1:**
[figure not shown]
Framework of the IMB model used in the study. HPV: human papillomavirus; IMB: information-motivation-behavioral skills.

We hypothesize that a digital HPV vaccination education intervention based on the IMB model will motivate parents to vaccinate their children against HPV, thus significantly improving the local HPV vaccination rate among 11-13-year-old girls (who are in the senior grade of primary school). Therefore, the primary objective of this study is to improve the HPV vaccination rate among 11-13-year-old girls in central and western China. Through this study, we aim to explore the potential influencing factors and mechanisms of parents’ hesitancy to vaccinate their daughters against HPV. In addition, we will discuss the intervention effects of 7-day digital HPV vaccination education based on the IMB model on the parents. The ultimate goal is to evaluate the efficacy of such intervention measures against HPV vaccine hesitancy in order to help improve the HPV vaccination rate among 11-13-year-old girls in China in the future.

## Methods

### Trial Design

This will be a double-blind randomized controlled trial (RCT) of an intervention based on an online applet. Before the intervention, the research team will carry out free HPV vaccination pilot projects for 11-13-year-old girls in 4-5 study sites in low-health-resource areas in China. After the first stage of the HPV vaccination program is completed, 11-13-year-old girls’ parents who choose not to vaccinate their daughters will be invited to our intervention study, and those who are willing to participate will be guided to register and log on to the “Yi Yan Health” mini applet (Figure 2), which was independently developed by our research team and can be used for mobile app–based education and questionnaire collection. Next, all participants will be randomly divided into 2 groups: (1) an intervention group, which will receive a baseline questionnaire, 7-day digital HPV vaccination education based on the IMB model (with a sample shown in Figure 3), and follow-up right after the intervention period and 1 week, 1 month, and 3 months after the intervention, and (2) a control group, which will only receive popular science education that is not related to HPV vaccines; these non-HPV publicity materials will be uploaded at the same time every day as the intervention group to maintain parents’ interest in the control group. Meanwhile, participants in the control group will also need to complete questionnaires simultaneously with the intervention group. After the intervention trial, we will provide the control group with the same IMB-based HPV vaccine intervention materials free of charge for ethical considerations. Our free HPV vaccination pilot program will also continue until at least half a year after the intervention to ensure that all 11-13-year-old girls whose parents are willing to vaccinate their daughters can receive the first HPV vaccination during or after the intervention.

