### Recruitment

In 5 regions with free HPV vaccination pilot projects, parents who refuse to vaccinate their daughters and who meet the inclusion criteria will be enrolled into this study. After providing informed consent, all participants will register and log on to the mini applet, and they will then be randomly assigned to the intervention group or the control group in a 1:1 ratio using the randomization algorithm embedded in the mini applet.

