According to the IMB model, digital HPV vaccination education is divided into 3 modules and 6 themes, with each module containing 2 themes. The first module is information, which is the initial prerequisite for promoting healthy behaviors. Module 1 has 2 themes: (1) HPV infection and related diseases and (2) high-risk factors of HPV infection and how to prevent HPV infection. The second module is motivation, which mainly refers to personal attitudes toward health behavior and related social motivation. Personal attitudes include the understanding of HPV susceptibility, the expectation of costs and benefits of taking preventive actions, and the experience and willingness to take actions; social motivation includes social support and social values. Module 2 has 2 themes: (3) introduce the benefits of HPV vaccines so as to encourage parents to vaccinate their daughters and (4) describe the harm and susceptibility of HPV infection through a true story to motivate parents to take action to prevent their daughters from contracting HPV infection. The third module is behavioral skills, which mainly emphasizes the improvement of personal objective skills and self-efficacy. Module 3 has 2 themes: (5) how to use personal objective skills to make firm decisions and communicate effectively with family members to obtain understanding and support for daughters’ HPV vaccination and (6) the concept and function of self-efficacy and ways to improve self-efficacy and promote the transformation of motivation into behaviors.

Each of the 6 thematic courses will be uploaded to the mini applet and will take participants about 10-15 minutes to read and learn. In addition, the mobile app–based HPV vaccination education contains a high level of interactivity with the following learning forms: reading text, viewing pictures, small videos pictures watching, and taking quizzes. The intervention will last for 1 week, and data will be collected at baseline ( 1 week before the intervention); postintervention; and 1 week, 1 month, and 3 months after the intervention. All the data will be obtained for statistical analysis.

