### Data Collection, Management, and Monitoring

The questionnaire will be distributed via the mini applet, and all completed questionnaires will be automatically saved into the read-only web-based database to ensure authenticity of the data. Moreover, our researchers will promptly check the collected data after each questionnaire survey. Regarding integrity of the data, all questions will be self-administered and set as mandatory to ensure that all submitted questionnaires have no missing data.

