### Statistical Analysis

Stata 16.0 will be used for statistical analysis. The distribution of categorical variables will be described by frequencies and percentages, and continuous variables conforming to normal distribution will be described by means (SDs). Chi-square tests will be performed to compare the differences between different groups. The *t* test or 1-way ANOVA will be performed to compare the mean scores between groups on the same continuous and dependent variables. Logistic regression will be conducted to analyze the factors associated with HPV vaccine hesitancy. Repeated measurement data at baseline; postintervention; and 1 week, 1 month, and 3 months after the intervention will be analyzed using generalized estimation equations (GEEs). Significant variables will be included in baseline chi-square analysis, and we will also assess group (intervention and control), time (baseline; immediately after the intervention; and 1 week, 1 month, and 3 months after the intervention), and time×group interactions, with the interaction indicating a differential change by group from baseline to the end of the trial. Statistical significance will be set at *P*<.05 (2-sided).

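### As written, parents are randomised at applet log-on and the baseline questionnaire comes afterwards, so the baseline of the questionnaire outcomes is not protected from possible knowledge of allocation or from loss after randomisation

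*Protocol article*

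**What the plan says.** The protocol article describes the sequence in three places.

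- **Trial Design.** Parents register and log on to the applet. Then: "Next, all participants will be randomly divided into 2 groups: (1) an intervention group, which will receive a baseline questionnaire". For the other arm, "participants in the control group will also need to complete questionnaires simultaneously with the intervention group".
- **Recruitment.** Once consent and log-on are complete, "they will then be randomly assigned to the intervention group or the control group in a 1:1 ratio". No questionnaire is mentioned before this step.
- **Intervention Group.** Measurement times are tied to the course and not to randomisation: "data will be collected at baseline ( 1 week before the intervention", followed by the post-intervention and later time points.

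Under Statistical Analysis, baseline is one of five time points in the generalised estimating equations (GEE), and the time-by-group term is read as the effect, "with the interaction indicating a differential change by group from baseline to the end of the trial".

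On blinding, the Blinding section and the Limitations both say that participants are not blinded. Trial Design and the Discussion call the trial double-blind, and the Blinding section also has participants unblinded once follow-up is over.

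**The concern.** In an individually randomised trial, baseline is normally measured before allocation, so that it cannot depend on the arm and everyone randomised has one. The order written here gives neither assurance.

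The secondary and other outcomes are self-reported scores: hesitancy, general attitudes, confidence and the IMB factors. A parent who knows the assigned arm may answer such items differently. If that happens at baseline, the error enters the change from baseline.

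The second risk does not depend on blinding. All items are mandatory, so a missing baseline means a whole questionnaire not submitted. Demographic data sit in the same instrument. A parent randomised at log-on who never submits it belongs to the intention-to-treat population promised in the Abstract, but has neither a baseline score nor questionnaire covariates.

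**Working it through.** **1. Order of events.** Trial Design gives log-on, random division, and then the baseline questionnaire as something the arm receives. Recruitment gives consent, registration, log-on and random assignment. It does not mention baseline, so it is consistent with Trial Design without independently confirming that baseline comes later. The Intervention Group section places baseline a week before the course and is silent on its relation to allocation. No shown text puts baseline first. The flowchart (Figure 4) and the SPIRIT schedule (Table S1) are not shown and might give another order.

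**2. Knowledge of the arm at baseline.** Participants are described as not blinded because of the nature of the intervention, but no course material is due until a week after baseline. No section says when parents are told their arm. Knowledge at baseline is possible and not established.

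**3. Outcomes exposed.** Under Primary Outcome, vaccination status is checked in health-agency registration records, so it does not use the baseline questionnaire. The exposed outcomes are the questionnaire scores analysed by GEE.

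**4. Size of a baseline shift (assumed values).** The only plan figure needed is the arm size: 5 sites × 150 = 750, and 750 / 2 = 375, as stated under Sample Size. Let B and F be the baseline and one follow-up mean, in SD units. The change contrast is

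D = (F_int − B_int) − (F_con − B_con).

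With no true effect and a shift s in one arm's baseline only, D is off by s in absolute value. If the same shift persisted at follow-up, it would cancel from D but remain in a comparison of follow-up scores.

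With n per arm and within-person correlation ρ, SE(D) = √(4(1 − ρ)/n). The false-positive rate at two-sided 0.05 is 1 − Φ(1.96 − s/SE) + Φ(−1.96 − s/SE).

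- n = 375, ρ = 0.5: SE = √(2/375) = 0.073. For s = 0.10, s/SE = 1.37 and the rate is 27.8%.
- n = 375, ρ = 0.7: SE = √(1.2/375) = 0.057. For s = 0.10, s/SE = 1.77 and the rate is 42.4%.

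| Assumed shift s | 375 per arm, ρ 0.5 to 0.7 | 300 per arm (375 × 0.8), ρ 0.5 to 0.7 |
|---|---|---|
| 0.05 SD | 10% to 14% | 9% to 12% |
| 0.10 SD | 28% to 42% | 23% to 35% |
| 0.20 SD | 78% to 94% | 69% to 89% |

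Neither s nor ρ is in the document. The table shows sensitivity and does not predict what will happen.

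**5. Size of the loss (assumed values).** At 5% non-completion, 0.05 × 375 = 18.75, about 19 per arm. If the whole 20% dropout allowance fell before baseline, 0.20 × 375 = 75 per arm. The document does not say when dropout is expected. These counts measure lost baselines and not bias. Bias would also require the loss to differ between arms in a way related to outcome.

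**The case against.** The strongest reply is that Trial Design is a summary of what each arm gets and not a timed procedure, and that the figures which would show the schedule are missing here. That is fair as a limit. It does not remove the point: the text has one literal order, nothing shown contradicts it, and if the flowchart differs the text still needs correcting.

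A reader might infer more than the document supports:

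- **That parents answer baseline knowing their arm.** Disclosure at randomisation is never stated, and one sentence delays unblinding until after follow-up.
- **That unblinded site assistants handle the baseline.** Their contact with participants is described for the intervention period. The questionnaire is self-administered: "The questionnaire will be distributed via the mini applet".
- **That missing baselines remove parents from the analysis.** A GEE with baseline as a response row keeps a parent's available follow-up rows. Parents would drop out only if questionnaire covariates were required, and the sentence on covariates is too unclear to settle that.
- **That every effect estimate is biased.** The vaccination outcome is untouched, and the planned chi-square and t tests between groups need no change from baseline.

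These objections stand. They reduce the point to a risk for the questionnaire outcomes.

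**Conclusion.** The point holds as a design weakness in the written sequence. Allocation at log-on, with the baseline questionnaire listed afterwards and participants described as not blinded, leaves the baseline of the hesitancy, attitude and IMB outcomes open to two avoidable problems: possible influence of the known arm, and randomised parents without a baseline score or questionnaire covariates.

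Its actual size cannot be computed from the document. Conditional on a shift confined to one arm's baseline, the change contrast is wrong by the full shift, and 0.10 SD would be enough to raise the false-positive rate well above 5% under the assumed correlations. Conditional on 5% non-completion, about 19 parents per arm lack a baseline. The conclusion rests on the shown text giving the intended order. It does not affect the primary vaccination outcome. It is worth correcting before launch because the remedy costs so little.

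**What to change.** Have the applet run its randomisation algorithm only after three steps are recorded: consent, the eligibility check and submission of the mandatory baseline questionnaire. Rewrite Trial Design and Recruitment in that order, and align the flowchart and the SPIRIT schedule if they differ. The eligibility check after consent is already described under Patient and Public Involvement, so only its place before allocation needs to be made explicit. In the same edit, reconcile the blinding statements in Trial Design, Blinding, Discussion and Limitations, and say when parents learn their arm.

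The cost is small. One applet both allocates and collects the questionnaires, and recruitment was still pending when the article was submitted. If the applet already takes baseline first, only the wording changes. The downside is that parents who do not complete baseline are not randomised, so somewhat more may have to be approached to reach 750.

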**Figure 2 figure2:**
[figure not shown]
Interface of the "Yi Yan Health" mini applet. IYH: Yi Yan Health mini-program.

